### Description of the interventions

#### Control group

Women in the control group will receive standard medical care during pregnancy and postpartum as dictated by their obstetricians. Any advice regarding infant nutrition or treatment of inverted nipples will be left to the primary physician, including possible use of the syringe technique, in which case the participant will continue in the study and will be analyzed in her group as dictated by the intention to treat principle. We will provide the participants in the control group with documentation on breastfeeding-associated complications, use of artificial devices to correct the inverted nipple, such as nipple shields, Niplette, inverted syringe, or breast pump, and the number of artificial milk feeds given to the newborn with their justification in a diary. The research assistant will send weekly reminders to the participants in the control group using e-mail, telephone messages, or communication through social media, to remind them about documentation in the diary.

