#### Intervention group

We will train the participants allocated to the experimental group on the use of the inverted syringe before each breastfeed as of the first postpartum day. We will also provide them with documentation on the daily use of the syringe, adverse events, breastfeeding-associated complications, use of artificial devices to correct the inverted nipple, the number of artificial milk feeds given to the newborn with their justification in a diary. The research assistant will send weekly reminders to the participants in the experimental group to use the syringe technique before each breastfeed using e-mail, telephone messages, or communication through social media. Syringe use will continue for as long as needed by the mother.

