### Outcome measures

#### Main outcome measure

The trial’s primary outcome is the difference between the two groups in the rates of exclusive breastfeeding at 1 month postpartum, whether breast milk is provided to the infant through direct latching on the mother’s breast or as expressed milk offered by cup or bottle.

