### Data collection

At baseline, we will collect information on socio-demographics such as maternal age, parity, education, employment, family monthly income, previous breastfeeding, and longest duration of previous breastfeeding if present. Data on gestational age, mode of delivery, newborn’s gender, birth weight, APGAR score, and nursery admission status (regular vs intensive care), as well as grading of maternal nipple inversion will be recorded.

On the first day postpartum, the following information will be collected: exclusive breastfeeding (yes/no), use of artificial milk (number of feeds in 24 h, justification), sore nipple (yes/no), pain while breastfeeding (yes/no), compliance with the use of the syringe technique before each breastfeed (experimental group only), and the use of other conservative methods to pull out the nipple (in both groups).

On the third and seventh days postpartum, we will call the participants to remind them about documentation in the diary, collect data about maternal breastfeeding evaluation (day 7 only), and address any questions.

The diary will be collected at 30 and 40 days during the participant’s postpartum visit to her obstetrician. We will also administer the Postpartum Quality of Life instrument, and collect data on the infant’s weight at month 1 from the infant’s health record. The eversion of the nipple will also be assessed by the research assistant during this visit.

On months 3 and 6 postpartum, we will call the participants to collect information on infant feeding methods, adverse events, and infants’ weight at 3 and 6 months.

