### Sample size

Based on data from a previous breastfeeding clinical trial that we conducted, 45% of women continue to breastfeed exclusively for 1 month postpartum [21]. We hypothesize that in women with inverted nipples, 40% of the experimental group and 5% of the control group will be exclusively breastfeeding at 1 month. To have 90% power and 5% type I error, and using the online calculator available at http://powerandsamplesize.com/Calculators/Compare-2-Proportions/2-Sample-Equality, we will need 25 women in each group to detect this 35% difference in the exclusive breastfeeding rates between the two groups.

In our recent breastfeeding support trial [21], the attrition rate was 40%. Since women with inverted nipples face more difficulties in breastfeeding than women with normally everted nipples, we hypothesize that 50% attrition rate would be a reasonable assumption for the proposed study. To account for a potential attrition rate of 50%, we inflated the sample size to become 100 women in total.

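### After the day 7 call only controls are reminded about the diary, the only 1-month feeding record described, and this could favour the syringe

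*Protocol article*

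**What the plan says.** Under Description of the interventions, the two arms have the same contact schedule: a weekly message from the research assistant by e-mail, telephone message or social media. The stated purpose differs.

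- **Control group:** the message is sent "to remind them about documentation in the diary".
- **Intervention group:** the assistant will "send weekly reminders to the participants in the experimental group to use the syringe technique before each breastfeed". The diary is not mentioned as a subject of this message.

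Under Data collection there is one diary prompt common to both arms: "On the third and seventh days postpartum, we will call the participants to remind them about documentation in the diary".

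In both arms the diary holds "the number of artificial milk feeds given to the newborn with their justification in a diary". Its return is described as follows: "The diary will be collected at 30 and 40 days during the participant’s postpartum visit to her obstetrician".

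The primary outcome is "the difference between the two groups in the rates of exclusive breastfeeding at 1 month postpartum". The section on the main outcome measure does not say which record it is taken from. For the later time points the source is explicit: "On months 3 and 6 postpartum, we will call the participants to collect information on infant feeding methods".

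**The concern.** The count of artificial milk feeds is what separates exclusive from mixed feeding. From the day 7 call until the diary is handed in at 30 to 40 days, one arm is prompted each week to write those feeds down and the other is prompted to do something else. A difference in prompting can become a difference in recording. If a feed that was never written down is taken as a feed that never happened, a mother who used formula appears as an exclusive breastfeeder, and this would happen more often in the arm that is not reminded.

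The outcome is self-reported in an open-label trial. Blinding the analyst, as Statistical methods plans, cannot correct data that were recorded differently by arm. The Discussion accepts detection bias as a consequence of open-label status, but this asymmetry does not follow from it: women who know their allocation can still receive identical diary reminders. The diary also carries complications and device use, so those comparisons are exposed in the same weeks.

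**Working it through.** **1. The plan's own figure.** Inputs from Sample size: "40% of the experimental group and 5% of the control group will be exclusively breastfeeding at 1 month", 90% power, 5% type I error (taken as two-sided) and 50% attrition.

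n per arm = [p1(1−p1) + p2(1−p2)] × [(z0.975 + z0.90)/(p1−p2)]²
= [0.40×0.60 + 0.05×0.95] × [(1.960 + 1.282)/0.35]²
= 24.66, rounded up to 25.

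25/(1−0.5) = 50 per arm, or 100 in total. The stated 25 and 100 reproduce. Nothing in this point changes them.

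**2. Diary prompts by period, as written.**

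| Period | Control | Experimental |
|---|---|---|
| Days 3 and 7 (calls) | diary | diary |
| Weekly messages | diary | syringe use |
| After day 7 until diary collection | diary, weekly | no diary prompt stated |

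**3. Where 1-month feeding status could come from.** Data collection lists feeding questions on day 1 and at months 3 and 6. For the postpartum visit it lists the diary, the quality-of-life instrument, infant weight and nipple eversion, but no feeding question. The diary is therefore the only 1-month feeding record described. That it supplies the primary outcome is an inference.

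**4. Size under stated assumptions.** Let p be the true exclusive rate, equal in both arms (no effect). Let u be the extra share of non-exclusive mothers in the syringe arm whose diaries show no formula feed and who are counted as exclusive. The documents give no value for u; 5% to 20% is assumed.

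Recorded rate, syringe arm = p + u(1−p)
Spurious difference = u(1−p)

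For example, with p = 5% and u = 10%: 0.05 + 0.10×0.95 = 14.5% against 5%, a difference of 9.5 points.

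The rejection probability is that of the uncorrected two-sided 5% chi-square test, by exact enumeration of both binomials.

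| True rate p | u | Spurious difference (points) | Rejection, 25 per arm | Rejection, 50 per arm |
|---|---|---|---|---|
| 5% | 0 | 0 | 2.0% | 4.3% |
| 5% | 5% | 4.8 | 7.6% | 13.5% |
| 5% | 10% | 9.5 | 19.7% | 36.5% |
| 5% | 20% | 19.0 | 52.2% | 82.3% |
| 20% | 0 | 0 | 5.5% | 5.2% |
| 20% | 5% | 4.0 | 6.8% | 7.8% |
| 20% | 10% | 8.0 | 10.7% | 15.6% |
| 20% | 20% | 16.0 | 25.1% | 43.4% |
| 40% | 0 | 0 | 6.0% | 5.2% |
| 40% | 5% | 3.0 | 6.7% | 6.5% |
| 40% | 10% | 6.0 | 8.7% | 10.0% |
| 40% | 20% | 12.0 | 16.2% | 24.1% |

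The 25-per-arm column matches the number the plan expects to analyse; 50 per arm assumes no attrition. Because the difference is u(1−p), it is largest when p is low. The 5% rows use the protocol's own control rate and are the least favourable shown. The other values of p are illustrative for a no-effect setting.

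**The case against.** A reader might infer that the diary supplies the primary outcome, that formula feeds will be recorded more fully in controls, and that the result will be biased towards the syringe. The documents do not support that much.

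- **Source.** No source is named for the primary outcome. The list for the postpartum visit is not exhaustive: latching at 1 month is a secondary outcome, yet it appears neither among the diary items nor in that list. The schedule figure is not available here and the article is condensed. A direct feeding question at the visit is possible. This stands.
- **Direction.** Bias towards the syringe needs a blank to be read as no formula. If incomplete diaries are treated as missing, the imputation in Statistical methods applies, with a sensitivity analysis with and without imputed data, and the sign is not fixed. This stands too, although that sensitivity analysis would not detect feeds left out of a diary that was returned.
- **Misclassification.** A mother must omit every formula feed that counts towards her 1-month status. One recorded feed is enough to classify her correctly. This is a reason to expect u to be smaller than the share of incomplete diaries.
- **Offsets.** Experimental women are also contacted weekly and log daily syringe use in the same diary, which may itself prompt recording. The wording does not rule out a diary prompt in the same message. The text does not show that either equals an explicit reminder.
- **Size.** u is an assumption, and every difference in the table is below the planned 35 points.

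These objections limit how firmly bias can be claimed. They do not remove the difference in reminder content, which is written separately for each arm and is not a detail left to a fuller document.

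**Conclusion.** The point holds as an avoidable risk of differential ascertainment; the documents do not demonstrate a bias. As written, after the shared calls on days 3 and 7 only controls are prompted to record artificial milk feeds.

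A distortion in favour of the syringe depends on three conditions: the diary determines 1-month exclusive breastfeeding, unrecorded feeds are read as none, and the missing prompt leaves more syringe-arm mothers with no formula recorded at all. If incomplete diaries are treated as missing instead, the direction is undetermined.

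The size cannot be derived from the documents. Under the assumed 5% to 20% with 25 per arm, the effect ranges from slight (6.8% rejection against 5.5% at a true rate of 20%) to serious (52% against 2% at a true rate of 5%). Severity: should-fix.

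**What to change.** 1. Send both arms the same weekly diary reminder, with the same wording, channel and day. Add the syringe prompt as a further sentence for the experimental arm only.
2. At the existing 1-month visit, ask the same direct question on infant feeding in both arms, and state whether this answer or the diary determines the primary outcome.
3. Report diary return and completeness by arm.

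The cost is one reworded message template, one question at a visit that already takes place, and a short table in the report. No extra contacts are needed and the sample size does not change. If the experimental message already covers the diary in practice, one clarifying sentence in the Intervention group section settles the first item.

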### Outcome measures

#### Main outcome measure

The trial’s primary outcome is the difference between the two groups in the rates of exclusive breastfeeding at 1 month postpartum, whether breast milk is provided to the infant through direct latching on the mother’s breast or as expressed milk offered by cup or bottle.

#### Secondary outcome measures

Secondary outcomes include differences between the two groups in the rates of nipple eversion at 1 month, successful latching of the infant on mother’s breast at 1 month, exclusive breastfeeding at 3 and 6 months, mixed feeding at 1, 3, and 6 months, breastfeeding-associated complications such as sore nipple, mastitis, pain, bleeding, and breast engorgement at 1 week, 1, 3, and 6 months postpartum. Other secondary outcomes are maternal satisfaction with breastfeeding assessed at 1 week postpartum using the validated Maternal Breastfeeding Evaluation Scale [18, 19], and maternal quality of life assessed at 1 month using the validated Postpartum Quality of Life instrument [20] (Fig. 1).

**Fig. 1 Fig1:**
[figure not shown]
Schedule of enrolment, interventions, and assessments

### Data collection

At baseline, we will collect information on socio-demographics such as maternal age, parity, education, employment, family monthly income, previous breastfeeding, and longest duration of previous breastfeeding if present. Data on gestational age, mode of delivery, newborn’s gender, birth weight, APGAR score, and nursery admission status (regular vs intensive care), as well as grading of maternal nipple inversion will be recorded.

On the first day postpartum, the following information will be collected: exclusive breastfeeding (yes/no), use of artificial milk (number of feeds in 24 h, justification), sore nipple (yes/no), pain while breastfeeding (yes/no), compliance with the use of the syringe technique before each breastfeed (experimental group only), and the use of other conservative methods to pull out the nipple (in both groups).

On the third and seventh days postpartum, we will call the participants to remind them about documentation in the diary, collect data about maternal breastfeeding evaluation (day 7 only), and address any questions.

The diary will be collected at 30 and 40 days during the participant’s postpartum visit to her obstetrician. We will also administer the Postpartum Quality of Life instrument, and collect data on the infant’s weight at month 1 from the infant’s health record. The eversion of the nipple will also be assessed by the research assistant during this visit.

On months 3 and 6 postpartum, we will call the participants to collect information on infant feeding methods, adverse events, and infants’ weight at 3 and 6 months.

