### Ethics approval

This study is approved by the Institutional Review Board (IRB) of the American University of Beirut. Written informed consent will be obtained from all participants. Since the study involves using the inverted syringe technique and documentation of relevant data in a diary, we estimate that the risks to women from participating in this study are negligible, not exceeding those of current standard practice. The only risk from nipple manipulation in the experimental group is the rare possibility of uterine contractions and labor induction if done prior to delivery. Since participants will start using the syringe right after delivery, this risk is eliminated. We also anticipate that the use of the syringe will result in less pain and less sore or bleeding nipples in the experimental group compared to the control group, who are at much greater risk for these complications secondary to poor infant latch. We will collect information on any adverse events during follow-up of participants, and will report all adverse events to the IRB as per institutional policies. Should any adverse events result directly from this study, the investigators’ institution will cover the cost of treating, on its premises, those medical adverse events.

Confidentiality of participants will be secured by storing the hard copies of the data collection forms in locked cabinets in the principal investigator’s office (MN). Access to electronic data stored in the SPSS data file will be password-protected, and restricted to the principal investigator (MN). The blinded analyst will be provided with a de-identified dataset to preserve confidentiality. Data will be stored for 5 years after publication of the study findings.

We will report any important modifications of the protocol to the IRB, trial participants, and trial registry. The trial’s results will be disseminated to healthcare professionals and the public through publication in a refereed journal, trial registry, and medical conferences.

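### The between-group pain and bleeding outcome does not clearly include symptoms caused by the syringe, so the comparison could be distorted in either direction.

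*Protocol article*

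**What the plan says.** Under Intervention group, women are trained in "the use of the inverted syringe before each breastfeed as of the first postpartum day", so suction comes before the feed. Their diary covers "documentation on the daily use of the syringe, adverse events, breastfeeding-associated complications". Under Control group, the diary covers "documentation on breastfeeding-associated complications, use of artificial devices to correct the inverted nipple" and artificial feeds; adverse events are not in that list.

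Secondary outcome measures compares the groups on "breastfeeding-associated complications such as sore nipple, mastitis, pain, bleeding, and breast engorgement at 1 week, 1, 3, and 6 months postpartum". Under Data collection, the day-1 items include "sore nipple (yes/no), pain while breastfeeding (yes/no"). No other pain item is worded. The month 3 and month 6 calls are said to collect feeding method, adverse events and infant weight.

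Ethics approval says "We will collect information on any adverse events during follow-up of participants", and the Abstract names adverse events among the secondary outcomes. Ethics approval also states an expected direction: "We also anticipate that the use of the syringe will result in less pain and less sore or bleeding nipples in the experimental group". That section attributes the controls' greater risk to poor latch, and the only risk it names for nipple manipulation is uterine contractions and labour before delivery.

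**The concern.** The syringe could change pain in two opposite ways: a better latch may prevent it, and suction may cause it. A fair comparison has to count both. An outcome labelled by its link to breastfeeding, with a worded item confined to the feed, plainly covers the first and leaves the second open. The separate adverse-events entry in one diary gives syringe users a second place to write the same symptom, outside the compared outcome.

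At stake is what the trial can say about tolerability. If suction pain is left out, a syringe that merely moves pain from the feed to the minutes before it could be reported as reducing pain. No later analysis can recover suction pain that nobody asked about.

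**Working it through.** **Plan's own figures.** The article gives no rate, power or sample size for pain. Its only calculation concerns the primary outcome and reproduces: (0.40×0.60 + 0.05×0.95)×(1.960 + 1.282)² / 0.35² = 24.66, so 25 per group, and 25/(1 − 0.50) = 50 per group after attrition. It has no bearing on pain; I use it only for the numbers per arm.

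**Where a symptom can be recorded**

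| Symptom | Day-1 form, both arms | Experimental diary | Control diary |
|---|---|---|---|
| Pain during a feed | pain item | complications | complications |
| Pain only during suction | no pain item fits | complications or adverse events; not stated | complications, if at all |
| Bleeding after suction | no item listed | complications or adverse events; not stated | complications, if at all |
| Lasting nipple soreness | sore-nipple item | complications | complications |

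The second and third rows are the problem. Controls can meet it too, since their physicians may advise the syringe or another device. At months 3 and 6 the calls list adverse events but not complications, so the boundary between the two entries matters there as well.

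All rates below are assumptions.

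**If suction pain is left out: break-even.** Let c and t be the proportions with feeding pain in the control and syringe arms, and s the proportion with suction pain among syringe women without feeding pain. Assume no device pain in controls. Total pain in the syringe arm is t + (1 − t)s, which equals c when s = (c − t)/(1 − t).

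| c | t | s at which the advantage vanishes |
|---|---|---|
| 40% | 30% | 0.10/0.70 = 14.3% |
| 50% | 40% | 0.10/0.60 = 16.7% |
| 60% | 40% | 0.20/0.60 = 33.3% |
| 60% | 30% | 0.30/0.70 = 42.9% |

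**If suction pain is left out: false claims.** Let total pain be 40% in both arms, and let a fraction f of the syringe arm's pain be missing from the compared outcome, so that the recorded rate is 0.40(1 − f). Exact enumeration of the uncorrected two-sided Chi-square test gives the probability of p < 0.05 in favour of the syringe:

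| f | Recorded rates, control v syringe | 50 per arm | 25 per arm |
|---|---|---|---|
| 0 | 40% v 40% | 2.6% | 3.0% |
| 0.10 | 40% v 36% | 6.2% | 5.5% |
| 0.25 | 40% v 30% | 17.9% | 12.1% |
| 0.50 | 40% v 20% | 59.5% | 35.1% |

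**Opposite direction.** Only women still breastfeeding can have pain at a feed. Let pain among them be q in both arms. The recorded difference, syringe minus control, is q × (proportion still breastfeeding with the syringe − proportion in control).

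- 80% v 50% still breastfeeding: 0.3×0.30 = 9 points at q = 30%; 0.5×0.30 = 15 points at q = 50%.
- 60% v 30%: again 9 and 15 points.
- Equal proportions: 0.

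Here the feed-tied wording counts against the syringe precisely when the syringe works as hoped.

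**The case against.** The case for leaving the text alone is substantial. Day 1 is not an outcome time point: the outcome is assessed at 1 week and at 1, 3 and 6 months, and there the word is simply pain. The complications can be read as a plain list of symptoms, so that a bleeding nipple counts whatever started it. Nothing asks mothers to assign a cause or makes the two diary entries mutually exclusive. The sore-nipple item is not confined to the feed. Exact form wording normally sits in the full protocol and the forms, which an article condenses, and Fig. 1 is not shown.

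Most of this stands, and it rules out three inferences a reader might draw:

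- **That less pain with the syringe is favoured by definition.** The wording omits a possible source of pain but does not fix the result. Suction just before a feed may carry over into it, and longer breastfeeding pushes the other way.
- **That harm from suction would go unreported.** Adverse events are collected and are a named secondary outcome.
- **That the Discussion also predicts less pain.** It anticipates fewer sore or bleeding nipples, less engorgement and less mastitis; pain appears only in Ethics approval, as an expectation and not as an analysis.

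What the objection does not answer is narrower. No sentence says that suction symptoms count in the compared outcome. Recording them as adverse events documents the harm but does not bring it into the pain comparison. The label and the one worded item are stated in the article, and both point to the feed.

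**Conclusion.** The point holds in a limited form. The pain and bleeding comparison does not clearly include symptoms caused by suction and may understate them in the syringe arm; a feed-tied item may equally overstate pain there if the syringe prolongs breastfeeding. The two effects cannot be assumed to cancel.

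The size is not derivable from the article. The false-claim figures rest wholly on an assumed 40% pain rate and an assumed share left out. They also require the affected women to have no other pain counted at that assessment, which is demanding: at a share of one tenth the false-claim rate is about double the no-omission rate, not many times it. The 9 to 15 points rest on assumed continuation and pain rates. These figures show only that either distortion could matter. The primary outcome is untouched.

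**What to change.** In both arms, on day 1 and at each outcome time point, ask in identical words about any nipple or breast pain and any nipple bleeding in the period, whatever the cause, with a tick for the occasion: feeding, syringe or other device. Define the secondary pain, soreness and bleeding outcomes by symptom, counting an entry from either the complications or the adverse-events section. Keep pain while breastfeeding as a component, so that the effect through latch stays visible.

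The cost is a few reworded form items and one outcome definition. Total pain is less specific to latch than feeding pain, which is why the component is kept. Recruitment began in June 2018, so women already enrolled have answered the existing wording; results can be shown by wording version.

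### After day 1, the diary collected at 30 and 40 days is the only stated record of first-month harms; the day 3 and day 7 calls list no harm question

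*Protocol article*

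**What the plan says.** The Data collection section gives the content of each contact in turn.

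- **Day 1:** sore nipple and pain while breastfeeding are asked directly, each as yes/no, beside feeding items and, in the syringe arm, compliance.
- **Days 3 and 7:** "we will call the participants to remind them about documentation in the diary, collect data about maternal breastfeeding evaluation (day 7 only), and address any" (the last: mothers' queries).
- **Postpartum visit:** "The diary will be collected at 30 and 40 days during the participant’s postpartum visit to her obstetrician". Quality of life, infant weight and nipple eversion are also obtained around this point.
- **Months 3 and 6:** telephone calls for which adverse events are named as an item.

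The diary differs by arm. In the Intervention group section it covers "documentation on the daily use of the syringe, adverse events, breastfeeding-associated complications, use of artificial devices to correct the inverted nipple". In the Control group section it covers "documentation on breastfeeding-associated complications, use of artificial devices to correct the inverted nipple, such as nipple shields, Niplette, inverted syringe, or breast pump" and artificial feeds; adverse events are not in that list.

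The weekly contacts are reminders. In the syringe arm, "The research assistant will send weekly reminders to the participants in the experimental group to use the syringe technique before each breastfeed"; in the control arm they prompt diary entries.

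Three other sections bear on this. Secondary outcome measures sets breastfeeding complications (sore nipple, mastitis, pain, bleeding, engorgement) as an outcome at 1 week and at 1, 3 and 6 months, and the Abstract also counts adverse events as a secondary outcome. In Ethics approval the investigators undertake to collect adverse events during follow-up and "will report all adverse events to the IRB as per institutional policies". In Sample size, "we hypothesize that 50% attrition rate would be a reasonable assumption for the proposed study", up from 40% in the team's earlier trial.

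**The concern.** The team speaks to the women twice in the first week, but the listed content of those calls leaves out the harms that the trial is committed to measuring and reporting. The day 7 call collects one 1-week outcome (satisfaction) and not the other (complications). Bleeding, mastitis or an injury from the syringe would be written in a diary that the team first reads at the postpartum visit.

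Two things are at stake. The first is oversight: the investigators cannot report to the IRB what they have not seen. The second is completeness: a diary informs the analysis only if it is handed in, and the Sample size section raises its attrition assumption precisely because these women have more trouble breastfeeding. The plan itself thus links drop-out to the kind of problem being counted.

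The analysis would not repair the loss. Statistical methods fills missing categorical values at random so as to keep the observed proportions, which would carry an understated complication rate forward. The stated sensitivity analysis for missing data concerns the primary outcome only.

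**Working it through.** **1. The plan's own figure.** The concern does not contest the sample size, but the attrition rate comes from there. Inputs: 40% versus 5%, 90% power, 5% type I error (taken as two-sided), 1:1 allocation.

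n = [p1(1−p1) + p2(1−p2)] × [(z for α/2 + z for power)/(p1−p2)]² = (0.24 + 0.0475) × [(1.960 + 1.282)/0.35]² = 24.66, so 25 per group. Allowing for 50% attrition, 25/(1 − 0.5) = 50 per group, 100 in total. The stated figures reproduce.

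**2. Where harms are recorded, by time, according to the text.**

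| Time | Stated source of harm data |
|---|---|
| Day 1 | Direct question: sore nipple, pain |
| Day 3 call | None listed |
| Day 7 call | None listed (satisfaction scale only) |
| Weekly messages | None listed (reminders) |
| Visit at 30 and 40 days | Diary handed in |
| Months 3 and 6 | Call: adverse events |

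Adverse events are named for the month 3 and 6 calls, and harm items for day 1. The two early calls have a list of their own without either.

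**3. Delay.** Delay = hand-in day − event day, with hand-in at day 30 to 40.

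- Event on day 3: 30 − 3 = 27 to 40 − 3 = 37 days.
- Event on day 5: 30 − 5 = 25 to 40 − 5 = 35 days.
- Event on day 7: 30 − 7 = 23 to 40 − 7 = 33 days.

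**4. Diaries that may not return.** At 50% attrition, 0.50 × 100 = 50 (25 per arm); at the earlier trial's 40%, 40 (20 per arm). Both are upper bounds: they suppose that every woman lost leaves before hand-in, and the protocol does not say when attrition occurs.

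**5. What such a loss could do (illustration; the risks and loss rates among affected women are assumed).**

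Even if loss is unrelated to harm, fewer events are seen. For an event with an assumed 5% risk per arm, the chance of seeing at least one is 1 − 0.95^50 = 92% with 50 diaries, 1 − 0.95^30 = 79% with 30, and 1 − 0.95^25 = 72% with 25.

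If affected women are lost more often, the observed rate is p(1 − d)/(1 − 0.5), where p is the true risk, d is the loss among affected women and overall loss is 50%. With p = 30%:

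- d = 60%: 0.30 × 0.40/0.50 = 24%.
- d = 70%: 0.30 × 0.30/0.50 = 18%.

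**6. Between arms.** Apply the same formula with d = 70% to assumed true risks of 40% in controls and 20% with the syringe. The observed rates are 0.40 × 0.30/0.50 = 24% and 0.20 × 0.30/0.50 = 12%. A true difference of 20 points in favour of the syringe shrinks to 12. Under these inputs the loss works against the syringe, so the direction of bias in the comparison cannot be read off the design.

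**The case against.** The strongest reply is that this argues from a short list in a condensed article. Fig. 1, the assessment schedule, is not available here and may show a 1-week complications assessment. Call forms and institutional adverse-event procedures may sit elsewhere, and Ethics approval does commit to collecting adverse events during follow-up. Part of this stands: the text cannot prove that no early harm question will be asked. But it does list what each call collects and names harms at other contacts, so followed as written it leaves the gap. If Fig. 1 does show such an assessment, the text still needs to match it.

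A second reply is that a diary filled in as events occur is a legitimate source for a 1-week outcome, and collecting it late does not change the entries. That is fair for diaries that come back. It answers neither the reporting delay nor the diaries that do not.

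A reader might infer three stronger things, none of which the document supports:

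- **That first-month harms are recorded only in the diary.** Sore nipple and pain are asked directly on day 1.
- **That harms in women who drop out are never seen.** A woman may volunteer a problem during a call, and those still reachable are asked about adverse events at months 3 and 6. Total loss applies to women who leave before hand-in, report nothing themselves and are not reached later.
- **That the gap biases the comparison in favour of the syringe.** The same diary route for complications serves both arms, and Ethics approval expects more pain and more sore or bleeding nipples in controls. Adverse events are listed only for the intervention diary, which could make harm look more frequent with the syringe.

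**Conclusion.** The concern holds in a limited form. Between day 1 and the visit at 30 and 40 days, the text offers only the diary for complications and adverse events, while committing to a 1-week complication outcome and to IRB reporting of all adverse events. The delay of 25 to 35 days for a day 5 event follows directly from the stated dates. The figure of up to 50 of 100 diaries rests on the plan's own attrition assumption and is a ceiling. The 18% and 24% illustrations rest on assumed inputs and show only that absolute harm rates could be clearly understated if affected women are lost more often.

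No direction of bias between the arms is established. The difference between the two diaries is a separate weakness: adverse events as listed are not captured alike in the two arms. The point deserves a change to the plan because the remedy uses contacts already scheduled; it does not affect the sample size.

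**What to change.** In Data collection, have the day 3 and day 7 calls ask every woman in both arms the same short checklist in fixed wording: sore nipple, pain, bleeding, mastitis, engorgement, any other adverse event. Record the answers on the call form and pass them on for IRB reporting under institutional policy. State that the day 7 answers, together with the diary, are the source for the 1-week complication outcome. List adverse events in the control diary as in the intervention diary, and align the text with Fig. 1.

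The cost is a few minutes per call, one form page and a minor amendment, with somewhat more events to report. There is one real drawback: answers taken by a research assistant in an open-label trial can be influenced by knowledge of the arm. Identical wording in both arms limits this, and keeping the diary as a second source allows the two to be compared.
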